## Methods

### Study design and setting

This observational prospective pilot study will be conducted in New York City Health + Hospital (NYC H+H)/Jacobi, New York, United States of America affiliated to Albert Einstein College of Medicine and Laikon General Hospital, Athens, Greece affiliated to National and Kapodistrian University of Athens. The study has been reviewed and approved from Biomedical Research Alliance of New York (BRANY) and the respective NYC H+H committee, as well as the ethics committee of Laikon General Hospital. Verbal informed consent will be obtained from all participants. Written consent was waived as POCUS is the standard of care and an integral part of physical examination in modern clinical medicine.

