### Population, Inclusion and Exclusion Criteria

We plan to include 120 men and women (at least 20 of them from the Laikon site) with the inclusion criteria consisting of patients ≥50 years of age, who undergo preoperative medical assessment for a major abdominal surgery under general anesthesia, have RCRI ≥2 (moderate or higher risk), and ASA-PS: II, III, IV (Table 1 and 2).

**Table 1. T1:** Revised Cardiac Risk Index (RCRI) for preoperative risk

RCRI clinical variable	Points
Elevated-risk surgery (intraperitoneal, intrathoracic, suprainguinal vascular)	1
History of ischemic heart disease	1
History of congenital heart failure	1
History of cerebrovascular disease	1
Preoperative treatment with insulin	1
Preoperative creatinine >2 mg/dL	1

**Table 2. T2:** American Society of Anesthesiologist's Physical Status (ASA-PS) - ASA classification

ASA Classification	Definition
ASA I	Normal healthy patient
ASA II	Patient with mild systemic disease
ASA III	Patient with severe systemic disease
ASA IV	Patient with severe systemic disease that is constant threat to life
ASA V	Moribund patient not expected to survive without operation
ASA VI	Declared brain dead patient whose organs are being removed for donor purposes

The exclusion criteria will be age <50 years, surgery other than major abdominal, anesthesia other than general, RCRI <2 points, and ASA-PS other than 2, 3, or 4.

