### Intervention

Included patients will undergo lung POCUS examination as part of their preoperative medical assessment prior to surgery. This is typically performed by an internal medicine specialist, and is usually done in a week to a few days in an outpatient clinic (in case of elective surgeries), and inpatient 0-1 days prior (in case of urgent surgeries). The studies will be performed by a sole operator (author LP), who was trained in POCUS during his internal medicine residency program, has attended POCUS courses via the American College of Physicians, and has been using POCUS on a daily basis in his clinical practice for more than five years. A single operator was chosen to eliminate the impact of inter-operator variability. POCUS images will be saved. To validate the findings, the operator's interpretation will be confirmed by an independent reviewer, who is a POCUS-trained critical care attending physician at NYC H+H/Jacobi (author PG). Clinicians will be blinded to lung POCUS findings, which is in-line with the high-quality POCUS literature [18]. Exceptions will include POCUS findings that are considered by the operator as critical, such as possible lung collapse, severe pulmonary edema, or large pericardial effusion, which will be reported to the clinicians.

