### Primary and Secondary Endpoints

The primary endpoint will be the composite of failure of extubation after surgery completion in the operation room with the need for re-intubation, unplanned use of continuous positive airway pressure (CPAP), bilevel positive airway pressure (BiPAP), or high-flow nasal cannula (HFNC) after postoperative extubation, admission to the intensive care unit for a primary cardiopulmonary etiology in the index admission, death from a primary cardiopulmonary etiology within 30 days from operation, or readmission for a primary cardiopulmonary etiology within 30 days from operation (whichever happens first). The secondary endpoints will be the individual components of the primary endpoint as above, the length of stay for patients discharged alive, the need for supplemental oxygen on post-operation day 1 in the surgery floor and the need for additional diagnostic tests or other interventions prior to the planned surgery as a response to critical POCUS findings. Length of stay is defined as the number of days from the day of the operation to the day when the patient is declared medically appropriate for discharge by the primary team.

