### Methodology of Analysis

The following 3 classifications of patients will be performed based on the iLUS: i) iLUS 0 vs. >0, ii) iLUS < mean iLUS vs. ≥ mean iLUS, iii) iLUS < median iLUS vs. ≥ median iLUS.

Continuous variables will be presented as mean with standard deviation and median with interquartile range. Categorical variables will be presented in absolute and relative frequencies. The appropriate parametric and non-parametric tests will be utilized for generating comparisons.

A sensitivity analysis will be performed for patients enrolled in the Jacobi site and patients enrolled in the Laikon site. Sensitivity analyses will be performed for various patient groups based on RCRI, ASA-PS, and AUB-HAS-2 scores, as well as whether the surgery was emergent or elective as deemed by the primary surgical team [23].

Multivariate analysis will be performed including iLUS classification and the following variables: age, sex, body mass index (BMI), RCRI, ASA-PS, and AUB-HAS-2 scores, time from POCUS scan to surgery, and emergent vs. elective surgery.

In addition, to preserve the integrity of our analysis while still reporting critical lung POCUS results, we will implement the following analysis: All patients enrolled in the study will be included in the primary analysis based on the intention-to-treat (ITT) principle to ensure that our results will reflect real-world practices. Patients with critical POCUS findings prompting interventions, postponement, or cancellation of surgery will be retained in the ITT analysis to maintain randomization integrity. Additionally, a pre-specified subgroup analysis will focus exclusively on these patients to evaluate the specific impact of the critical POCUS results on outcomes such as completion of surgery, postoperative complications, intensive care unit admission, mortality, length of stay, and readmissions. To further assess the robustness of our findings, a sensitivity analysis will be conducted, excluding patients with critical findings to evaluate the effect of blinding on the study outcomes.

An interim analysis will be performed after the follow-up completion of 60 participants (with at least 10 participants at the Laikon site). Should the interim analysis reveal findings that decisively confirm or reject the study hypothesis, no more participants will be enrolled, and the study will be ended after the follow-up completion of the last enrolled participant.

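### The two critical-finding analyses cannot show the impact of critical results or the effect of blinding, because only patients with critical findings are unblinded and they have no comparator

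*Protocol article*

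**What the plan says.** The design is a single observational cohort: "This observational prospective pilot study will be conducted in New York City Health + Hospital" and at a second site in Athens, with 120 patients planned. All of them are scanned: "Included patients will undergo lung POCUS examination as part of their preoperative medical assessment prior to surgery" (Intervention).

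The same section sets the blinding rule, "Clinicians will be blinded to lung POCUS findings", and its exception: "Exceptions will include POCUS findings that are considered by the operator as critical". The safety section repeats that findings the operator considers critical go to the primary team.

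Methodology of Analysis keeps all patients in the primary analysis, including those whose critical findings led to an intervention, a postponement or a cancellation. It then adds two analyses:

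- For the patients just described, "a pre-specified subgroup analysis will focus exclusively on these patients to evaluate the specific impact of the critical POCUS results on outcomes". The listed outcomes include completion of surgery, postoperative complications, intensive care admission, mortality, length of stay and readmission.
- A sensitivity analysis, introduced as a check of robustness, "excluding patients with critical findings to evaluate the effect of blinding on the study outcomes".

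**The concern.** Both analyses carry a causal aim. To learn what a reported critical result does to outcomes, one needs similar patients whose critical result was not reported. To learn what blinding does, one needs blinded and unblinded patients of comparable severity. The protocol describes neither.

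This matters because of the study's hypothesis. Aims and Hypothesis states that early lung POCUS can reduce postoperative complications. With clinicians otherwise blinded, a reported critical finding is the only route the article describes by which the scan could change care. Readers will therefore look to these two analyses for a causal answer, and the Conclusion hopes that the results will inform randomized trials and guidelines. Followed as written, the plan would attach causal conclusions to a subgroup without a comparator and to an exclusion that removes the severe-looking and the unblinded patients together.

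**Working it through.** The article gives no expected number of critical findings, event rate or effect size for these analyses, so there is no figure to reproduce. The question is whether the effects can be identified at all.

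**Step 1: cross-classify the patients by the stated rules** (Intervention; Safety, Adverse Events Definition, and Reporting).

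| | Clinicians blinded | Clinicians told |
|---|---|---|
| Critical finding | none planned | all |
| No critical finding | all | none planned |

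Two of the four cells are empty by design. The probability of unblinding is 1 given a critical finding and 0 otherwise. There is also no unscanned group.

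**Step 2: the exclusion analysis.** Let c be the share with critical findings, p0 the event risk without a critical finding, and p1 the observed risk in critical (hence unblinded) patients. Then:

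- risk in all patients = c × p1 + (1 − c) × p0
- risk after exclusion = p0
- shift = c × (p1 − p0)

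The effect of reporting in critical patients is p1 − pB, where pB is their risk had their clinicians stayed blinded. pB is never observed and does not appear in the shift.

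**Step 3: numbers.** All rates are assumptions; only N = 120 is from the protocol. Take c = 10% (12 critical, 108 not), p0 = 10% and p1 = 30%.

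- All patients: 0.10 × 30% + 0.90 × 10% = 12.0%
- After exclusion: 10.0%
- Shift: 0.10 × (30% − 10%) = +2.0 points

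| Unobserved pB | Effect in critical patients | Effect over the cohort (c × effect) | Shift seen |
|---|---|---|---|
| 30% | 0 points | 0 points | +2.0 points |
| 40% | −10 points | −1.0 point | +2.0 points |
| 60% | −30 points | −3.0 points | +2.0 points |

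The observed data are the same in all three rows. If the higher risk with the unblinded patients included were read as the effect of unblinding, it would point to harm in the two rows where reporting helps. Keeping p1 at 30%, and varying c from 5% to 15% and p0 from 10% to 20%, the shift runs from 0.05 × (30% − 20%) = +0.5 points to 0.15 × (30% − 10%) = +3.0 points. It never depends on pB.

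The crude risk is used for simplicity. Because the observed data do not change with pB, any statistic computed from them, including an adjusted iLUS-outcome association, is equally uninformative about it. More patients would estimate the shift more precisely but would not reveal pB.

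**Step 4: the subgroup analysis.** It contains only critical patients whose finding prompted an action, so all of them are unblinded and there is no contrast within it. Patients without critical findings are no substitute, because they differ in severity as well as in blinding. Critical patients whose finding prompted nothing are unblinded too, and a comparison with them is not planned.

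The selection also acts on one listed outcome. A patient can enter the subgroup because surgery was cancelled or postponed, while a critical patient who went to surgery with no change of plan is left out. The proportion completing surgery is therefore partly determined by the entry rule.

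**The case against.** The strongest reply is that the sentence on exclusion opens by naming robustness as its purpose. On that reading the plan asks only whether the main association survives when patients with unblinded clinicians are removed, which is a standard and sound check. Likewise, the subgroup has no test or effect estimator attached, and what happened after a critical result can be described without a control group. This stands as a defence of running both analyses. It does not rescue the aims, because the article goes on to say what each analysis is meant to evaluate, and the design cannot deliver either. A separate analysis plan could not supply the missing comparator. Pilot status excuses imprecision, not an effect that cannot be identified.

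The article speaks of the impact of critical results, not of reporting them. Reading it as the impact of reporting is a paraphrase, though a fair one, since the paragraph is about reporting such results and the subgroup is defined by the actions they prompted.

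Three stronger readings are tempting, and the document does not support them:

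- A reader might infer that the secondary endpoint on "the need for additional diagnostic tests or other interventions prior to the planned surgery as a response to critical POCUS findings" will be compared across iLUS groups, a circular comparison. No section states such a comparison, and a simple count of these actions is legitimate.
- A reader might infer that excluding critical patients cuts off the top of the iLUS range. Critical status is the operator's judgement, not a score threshold. A pericardial effusion of any size scores 1 point out of 40 (Table 3), so a patient with a large one could have a low total.
- A reader might take the small size of the subgroup as the measure of the problem. The article gives no expected count, and wide intervals would show imprecision, which is a different fault.

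**Conclusion.** The point holds for the two stated aims. Under the article's own blinding and reporting rules, neither the specific impact of critical results nor the effect of blinding can be estimated, whatever the sample size. The completion-of-surgery outcome is additionally compromised by how the subgroup is selected.

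This rests on the rules being followed as written: every finding called critical is reported, and no other route of unblinding exists. The article describes no other. The conclusion does not depend on the assumed rates, which serve only to illustrate it.

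The reach is limited. The primary analysis, endpoints, sample size and data collection are untouched, and both analyses remain worth doing under a different description. It should still be corrected, because it determines what the study may conclude about whether the scan changes outcomes.

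**What to change.** In Methodology of Analysis:

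- Make the subgroup of patients whose critical findings prompted action descriptive only: number of patients, actions taken and outcomes observed, with no causal claim. State that completion of surgery is partly determined by how the subgroup is chosen.
- Keep the analysis that excludes patients with critical findings, but define it as a robustness check of the iLUS-outcome association among patients whose clinicians stayed blinded.
- Delete the specific impact of critical results and the effect of blinding as aims.

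The cost is a change of wording. No data, patients or analyses are added or lost; two causal claims that the design cannot support are given up.

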## Aims and Hypothesis

We aim to study the value of adjunctive iLUS at the time of preoperative medical assessment by internal medicine physicians on postoperative cardiopulmonary outcomes. Our primary hypothesis is that early lung POCUS assessment in moderate- to high-risk adult patients over 50-years-old undergoing abdominal surgery can reduce postoperative complications, thereby decreasing intensive care unit admissions, mortality, hospital length of stay, and readmissions.

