The statistical significance threshold will be set at p ≤0.05. Analysis will be conducted with STATA software (version 14.1, STATA corporation, College Station, TX, USA).

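### The interim look at 60 of 120 patients can end enrolment in either direction on an undefined criterion, with p ≤0.05 as the only threshold and no named iLUS test

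*Protocol article*

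**What the plan says.** Three statements in Methodology of Analysis matter here.

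- **Timing.** "An interim analysis will be performed after the follow-up completion of 60 participants (with at least 10 participants at the Laikon site" and so on. Population, Inclusion and Exclusion Criteria gives the full size: "We plan to include 120 men and women (at least 20 of them from the Laikon site". The look therefore falls at half the planned sample.
- **Action.** "Should the interim analysis reveal findings that decisively confirm or reject the study hypothesis, no more participants will be enrolled". The study then closes once those already enrolled complete follow-up. The stop works in both directions.
- **Threshold.** "The statistical significance threshold will be set at p ≤0.05". This is the only decision level in the document, and it does not separate interim from final.

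The comparison is not fixed either. "The following 3 classifications of patients will be performed based on the iLUS: i) iLUS 0 vs. >0", followed by a split at the mean and a split at the median. None of the three is called primary. The hypothesis to be confirmed or rejected, in Aims and Hypothesis, is that "early lung POCUS assessment in moderate- to high-risk adult patients over 50-years-old undergoing abdominal surgery can reduce postoperative complications".

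**The concern.** A stop that depends on outcome data needs three things: a test, a limit for that test, and a final analysis that allows for the first look. The plan commits to the action but gives none of the three. Whoever sees the interim data can choose the split and decide how strong is strong enough after seeing the result.

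The two directions carry different risks. Stopping to confirm can raise the type I error above the stated 5%. Stopping to reject could end the study on data too sparse to tell no association from a sizeable one. Either would mislead the larger randomised trials that the Conclusion hopes to inform.

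The trigger also fits its target poorly. The stated hypothesis concerns what scanning does to complications, but the analysis compares iLUS groups among patients who were all scanned. No comparison planned at either look tests the hypothesis as worded, so the plan does not show what result would count as confirming it.

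**Working it through.** **Inputs.** The information fraction is 60/120 = 0.5. The level is 0.05; sidedness is not stated, and two-sided is assumed. Three iLUS splits are planned. The plan gives no event rate, effect size, iLUS distribution, power or overall error rate, so it has no figure to reproduce. Values assumed below are marked as such.

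**1. Type I error of one test over two looks.** Under no association, the statistics Z1 (60 patients) and Z2 (120 patients) are standard bivariate normal with correlation √0.5 = 0.707. The overall error is P(|Z1| > c1 or |Z2| > c2). With the final test left at 0.05 (c2 = 1.960):

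| Interim level | c1 | Overall error |
|---|---|---|
| 0.05 | 1.960 | 0.083 |
| 0.01 | 2.576 | 0.055 |
| 0.005 | 2.807 | 0.052 |
| 0.001 | 3.291 | 0.0502 |

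The first row applies the only written threshold at both looks. The others show what a stricter, unwritten reading would give.

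**2. What a null-looking result at 60 can show.** An effect with 80% power at 120 has expected Z2 = 1.960 + 0.842 = 2.802. Its expected Z1 is 2.802 × 0.707 = 1.981. The chance of significance at 60 is Φ(1.981 − 1.960) = 0.51, so it is non-significant in 49% of studies. For 90% power, expected Z1 is (1.960 + 1.282) × 0.707 = 2.292, and it is non-significant in 37%. Neither figure needs an event rate.

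As an example, assume risks of 15% and 30% in equal groups of n each. Power = Φ[(0.15 − 1.96·s0)/s1], with s0 = √(2 × 0.225 × 0.775/n) and s1 = √((0.15 × 0.85 + 0.30 × 0.70)/n).

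- n = 30 (60 patients): s0 = 0.1078, s1 = 0.1061; Φ(−0.578) = 0.28. Expected events are 4.5 + 9 = 13.5.
- n = 60 (120 patients): s0 = 0.0762, s1 = 0.0750; Φ(0.008) = 0.50.

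Other assumed risks, power at 60 and at 120: 10% v 20%, 0.19 and 0.33; 20% v 40%, 0.39 and 0.67; 10% v 30%, 0.49 and 0.79.

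**3. Three splits, kept apart from the interim look.** Null trials were simulated with assumed skewed iLUS distributions (15% to 55% of patients scoring 0), assumed event rates of 15% to 25%, and uncorrected chi-square tests at 0.05. Any of the three splits was allowed to count.

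- One analysis at 120, no interim look: about 9% to 12%, and near 8% in some runs with 55% of patients scoring 0.
- Looks at 60 and 120: about 13% to 20%.

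The low end comes from the case where most patients score 0. The median is then 0, and the median split puts everyone in one group.

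**4. Check of the proposed limits.** Solving the integral in step 1 with c1 = √2 × c2 for an overall 0.05 gives c1 = 2.797 (p = 0.0052) and c2 = 1.977 (p = 0.048). The rounded limits 0.005 and 0.048 give an overall 0.0499.

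**The case against.** The strongest reply is that the plan nowhere says p ≤0.05 triggers the stop. It asks for decisive findings, which in ordinary reading is stricter than plain significance, and a strict interim level costs almost nothing (5.02% at 0.001). Numerical boundaries are also commonly left to an analysis plan, and this is a condensed article about a pilot that claims no power. Much of this stands. The 8.3% is the upper case for one test, and the absence of a boundary table would not by itself be a finding. What remains is that the article fixes a two-way stop on an undefined term, beside one undivided threshold and with no test named.

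Two stronger readings are tempting, and the documents support neither.

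- A reader might infer that the interim look pushes the error to nearly 20%. Half or more of that figure comes from testing three splits and would remain with no interim look. Nor does the plan say that any one split may trigger the stop.
- A reader might infer that the reject stop would often end a study with a true association, because the 15% v 30% example is non-significant at 60 in 72% of cases (1 − 0.28). That is the chance of p >0.05 under assumed risks. The chance of stopping cannot be computed from the written rule, and the same example has only 50% power at the full 120, so part of the shortfall is the pilot's size.

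The low risk of ultrasound scanning is likewise no proof of error. It means only that safety gives little reason to stop early.

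**Conclusion.** The point holds as a badly fixed decision rule. The plan commits to stopping at half the data without defining the criterion or naming the test.

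The error for a single test lies between about 5.0% and 8.3%, according to the interim level actually used. This assumes a two-sided test, half information and a final test left at 0.05. Multiplicity across the three splits is a separate problem that depends on assumed score distributions and event rates. In the reject direction, a non-significant result at 60 is weak evidence of no association, and this does not depend on how strictly the criterion for confirming is read.

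The plan should be changed before the 60-patient data are examined. The fault does not invalidate the study, and if enrolment runs to 120 without an outcome-based decision at 60, no error is added by the interim look.

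**What to change.** **Preferred.** Remove the outcome-based stop. Use the 60-patient look for feasibility, data quality and the event rate pooled over iLUS groups, and leave the final level at 0.05.

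**If stopping is kept.**
- Name one primary iLUS comparison on the composite endpoint and tie the stop to it alone.
- Apply two-look O'Brien-Fleming limits: p ≤0.005 at 60 and p ≤0.048 at 120.
- Drop the stop to reject, or make it non-binding with a stated conditional-power limit.
- Restate the hypothesis that the stop refers to as the association that is actually tested.

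Naming a primary comparison is worthwhile under either option, because removing the stop does not cure the multiplicity across the three splits.

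**Cost.** The text change is short. Under the second option the final threshold moves from 0.050 to 0.048. Early ending becomes less likely under either option, so the study will usually run to 120. Choosing one iLUS comparison from three is a real design decision and has to be made before outcomes are seen.
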